Participants who were randomized to CBT, LT, or CBT+LT and who had not dropped out of the study by the end of acute treatment phase were invited to return to the laboratory for a naturalistic follow-up visit during the subsequent winter season (i.e., in January or February when SAD symptoms are typically at their worst). The follow-up report [11] was an ITT analysis of all randomized participants based on multiple imputation to estimate next winter outcomes for the 17 randomized individuals who dropped out during treatment, were withdrawn from protocol, or were lost to follow-up. The CBT (7.0%) and CBT+LT (5.5%) groups had significantly smaller proportions of winter depression recurrences than the LT group (36.7%). Solo CBT, but not combination treatment, was also associated with significantly lower interviewer- and patient-rated depression severity the next winter as compared to solo LT. Among completers who provided follow-up data, all statistically significant differences between the solo CBT and LT groups persisted after adjustment for ongoing treatment with LT, antidepressants, and psychotherapy. In contrast, CBT+LT and LT groups did not differ on next winter outcomes after adjustment for ongoing treatments. Therefore, despite having the highest post-treatment remission rate, initial treatment with combined CBT+LT did not appear to show the same lasting benefit over solo LT treatment on next winter outcomes as initial treatment with solo CBT. Observed differences between solo CBT and solo LT the next winter (i.e., a 30% difference in depression recurrence and 6- to 7-point differences in continuous depression scores) were large, clinically meaningful, and apparently not secondary to ongoing treatment use. Therefore, these findings require replication in a larger, more definitive study to determine whether CBT represents a more effective, practical approach to long-term SAD management than LT.

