### Sample size and statistical power

This RCT is designed to definitively test for a significant and clinically meaningful difference between CBT and LT on depressive episode recurrence during the next winter season (the primary endpoint). The true difference between CBT and LT (and the difference we observe in this more rigorous design) may be smaller than what was observed in the above pilot study. To determine sample size, the more conservative estimate of a 23% difference in recurrence was used, based on a worst case scenario assumption that all subjects who dropped out of the pilot studies at any time from randomization through the next winter follow-up would have evidenced a recurrence the next winter (52% in LT vs. 29% in CBT in the ITT sample). If the true difference is 23%, 80 participants per group (total *N* = 160) are required to provide 80% power to detect a significant difference in recurrence between CBT and LT with a 2-sided test and alpha = 0.05. With 80 participants per group, there is also 80% power to detect a 5-point difference in next winter continuous depression scores based on variance estimates from a worst-case scenario analysis of pilot data whereby pre-treatment scores were substituted for any missing next winter scores (14.3 ± 11.5 for CBT vs. 19.5 ± 11.5 for LT on the Structured Interview Guide for the Hamilton Rating Scale for Depression—Seasonal Affective Disorder Version).

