### Data analysis plan

The primary analysis is an intent-to-treat (ITT) analysis based on multiple imputation (MI) of missing next winter SIGH-SAD scores [39-41]. Imputed scores will be used to classify depression recurrence status for individuals who dropped out during the treatment phase, were withdrawn from protocol, or were subsequently lost to follow-up. Imputed values will be generated from multivariate normal models derived from subjects with next winter follow-up data, using baseline and post-treatment SIGH-SAD, HAM-D, and atypical scores, demographic variables (e.g., gender, race, age), and other baseline patient characteristics (e.g., presence of a comorbid axis I disorder, antidepressant medication status) as potential predictors. Separate models will be developed for the CBT and LT groups rather than including treatment group in the model as a predictor, because in the pilot study, baseline SIGH-SAD scores were negatively correlated with next winter scores in CBT and were positively correlated with next winter scores in LT. Outcomes for subjects with missing next winter data will be predicted from the models based on available data and a random component reflecting the residual distribution for the dependent variable. Ten data sets with different imputed values will be generated, and a dichotomous variable indicating recurrence status will be computed for each subject based on SIGH-SAD criteria. The difference between the CBT and LT groups in the proportions of subjects with a recurrence the next winter will be estimated for each of the ten data sets and the estimates will be combined using the inference methods for MI described by Little and Rubin [42]. SAS PROC MI and PROC MIANALYZE will be used to carry out the imputation and analysis. Sensitivity analysis will be conducted to determine the robustness of the results under alternative MI models and imputation methods, including best and worst case scenarios for each treatment.

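### Ten imputations are valid for the primary recurrence test but leave avoidable seed-to-seed noise in a borderline p-value; at least 100 would cut it about threefold for computing time only

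*Protocol article*

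**What the plan says.** The Data analysis plan states: "The primary analysis is an intent-to-treat (ITT) analysis based on multiple imputation (MI) of missing next winter SIGH-SAD scores". Imputed scores are then classified as recurrence or no recurrence by the SIGH-SAD criteria. On the imputation model it says: "Separate models will be developed for the CBT and LT groups rather than including treatment group in the model as a predictor". The number of imputations is set by "Ten data sets with different imputed values will be generated", and the difference in recurrence proportions "will be estimated for each of the ten data sets and the estimates will be combined using the inference methods for MI". The same analysis is to be repeated for three alternate recurrence definitions, which therefore inherit the ten imputations.

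The planned sensitivity analyses vary the imputation model and method and include best and worst cases. They do not vary the number of imputations.

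The article gives no expected missing-data rate for this trial. Under Sample size and statistical power, the planning rates are "52% in LT vs. 29% in CBT in the ITT sample", obtained by counting every pilot dropout as a recurrence. Under Pilot and feasibility studies, the multiple-imputation recurrence rates are 36.7% for LT and 7.0% for CBT.

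**The concern.** Multiple imputation uses random draws, so a rerun with another seed gives a slightly different pooled difference, standard error and p-value. The size of that variation depends on the fraction of missing information (FMI) and on the number of imputations, m. Relative efficiency, the usual argument for a small m, describes variance over repeated trials. It does not say how far the p-value of one fixed data set moves between seeds.

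The trial has a single primary endpoint, tested two-sided at 0.05 and planned for 80% power, so a result near the boundary is possible. There, the seed could settle which side of 0.05 is reported. The noise falls with a larger m, and m is a number the plan states outright.

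**Working it through.** **1. The plan's own figure.** The inputs are 52% vs 29% (difference 0.23, mean 0.405), two-sided alpha 0.05 and 80% power.

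- Without continuity correction: n = [1.96·√(2·0.405·0.595) + 0.8416·√(0.52·0.48 + 0.29·0.71)]² / 0.23² = (1.361 + 0.568)² / 0.0529 = 70.3, so 71 per arm.
- With continuity correction: n = (70.3/4)·[1 + √(1 + 4/(70.3·0.23))]² = 78.8, so 79 per arm.

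The stated 80 per arm is reproduced to within one participant.

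**2. Missingness (an assumption, shown as a range).** If a share d is missing and all of it is counted as recurrence, the worst-case rate is w = r(1 − d) + d, where r is the rate among those followed. Hence d = (w − r)/(1 − r).

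- LT: (0.52 − 0.367)/(1 − 0.367) = 24.2%
- CBT: (0.29 − 0.07)/(1 − 0.07) = 23.7%

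This takes the pilot multiple-imputation rates as rates among those followed. About 24% is used as the upper value and 10% as a lower one.

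**3. Efficiency.** Relative efficiency = 1/(1 + FMI/m). With FMI 0.24 it is 1/1.024 = 97.7% at m = 10 and 1/1.0024 = 99.8% at m = 100.

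**4. Movement of the test statistic between seeds.** Over seeds, the pooled difference has variance B/m, where B is the between-imputation variance. Dividing by the total variance gives SD(z) ≈ √(FMI/m). A result at exactly z = 1.96 then has a 95% range over seeds of 1.96 ± 1.96·SD(z).

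| FMI | m | SD(z) | range of p |
|---|---|---|---|
| 0.24 | 10 | 0.155 | 0.024 to 0.098 |
| 0.24 | 100 | 0.049 | 0.040 to 0.062 |
| 0.10 | 10 | 0.100 | 0.031 to 0.078 |
| 0.10 | 100 | 0.032 | 0.043 to 0.058 |

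**5. Simulation on fixed data.** There are 80 per arm with 61 observed and 19 missing in each, arm-specific binary imputation with a posterior draw, Rubin's rules and 20,000 seeds. The SD of the pooled difference over seeds is 1.32 percentage points at m = 10 and 0.42 at m = 100. Take a data set whose p with 1000 imputations is about 0.037. At m = 10 the central 95% of seeds gives p = 0.015 to 0.097, with 33% of seeds above 0.05. At m = 100 it gives 0.028 to 0.051, with 3% above.

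**6. Simulation over whole trials.** Each simulated trial is analysed with two seeds. The table gives the share of trials in which the two disagree on p < 0.05.

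| True rates, LT vs CBT | Missing | m = 10 | m = 100 |
|---|---|---|---|
| 52% vs 29% (design) | 24% | 7.3% | 2.1% |
| 52% vs 29% (design) | 10% | 3.5% | 1.0% |
| 44% vs 29% | 24% | 8.8% | 2.5% |
| No difference | 24% | 2.6% | 0.7% |
| 36.7% vs 7.0% (pilot) | 24% | 0.7% | 0.2% |

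At the design rates with 24% missing, power is 73.5% at m = 10 and 74.6% at m = 100. Type I error at m = 10 is 5.4%. A version closer to the plan imputes normal scores by arm from a predictor with correlation 0.5 and dichotomises at a total of 20. It gives 6.2% and 1.7% disagreement at 24% missing.

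**The case against.** The strongest reply is that nothing in the plan is wrong. Rubin's rules include the B/m term, so ten imputations give a valid test and interval, and the efficiency and power losses are trivial. This stands.

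A reader might go further and infer that the seed will decide the trial. Among simulated data sets picked because their converged p lay between 0.032 and 0.054, 16% to about 60% of reruns fell on the other side of 0.05. Those figures are conditional on an already borderline result. The unselected figure at the design rates is 7.3% with 24% missing and 3.5% with 10%. At an observed 23-point difference, 99.8% of seeds stay significant with m = 10.

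A reader might also infer that a second analyst could not reproduce the result. A recorded seed makes it exactly reproducible at any m. Recording the seed is commonly left to the statistical analysis plan or the program, so its absence here is no finding.

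Two further objections hold in part. The 24% is not stated for this trial, and the pilot rates behind it come from an analysis of all randomized participants, imputed values included; hence the range down to 10%. And 100 imputations do not abolish seed dependence, since a result at p = 0.05 still spans 0.040 to 0.062.

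What the reply does not remove is that a smaller noise is available at no cost to participants or design. The planned sensitivity analyses do not measure this noise, because none of them varies m.

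**Conclusion.** This is a free improvement, not an error. Ten imputations leave the primary estimate unbiased and the test valid. They leave avoidable Monte Carlo noise that matters only when the result is near 0.05. Going from ten to 100 cuts seed disagreement on the primary conclusion about threefold.

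These sizes rest on an assumed 10% to 24% missing next-winter outcomes, the article's design rates, 80 per arm and a simplified imputation model. The document does not support a claim that the primary analysis is invalid or that its outcome generally turns on the seed.

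**What to change.** In the Data analysis plan, replace ten imputed data sets with at least 100 for the primary recurrence analysis, and carry the same number through to the three alternate recurrence definitions. Report the Monte Carlo error of the pooled difference, √(B/m), beside the estimate, so that readers can judge whether a borderline result is stable.

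The cost is computing time for 160 participants. Recruitment, visits, assessments, the endpoint and the effect measure are unchanged.

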### Randomization procedure

Participants are randomly allocated to one of the two equal-probability, parallel, concurrent study treatments on a continuous basis as they qualify for the study. The schedule was designed by the project biostatistician/co-investigator ([name]) and was reviewed by an independent statistician prior to initiating the study. It was based on permuted random-size blocks of four and six, stratified by three variables: (1) sex, (2) major comorbid axis I diagnosis with two levels (present/absent), and (3) current antidepressant medication status with two levels (on medication or not). The randomization schedule is not available to anyone except the project statistician. Only the project coordinator, who does not conduct any assessments related to treatment outcome, is permitted to randomize participants.

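### The primary risk difference has no term for the three randomisation strata: the analysis is valid, but some precision is lost if those factors predict recurrence

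*Protocol article*

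**What the plan says.** The protocol article, under Randomization procedure, describes permuted blocks of four and six with equal allocation, "stratified by three variables: (1) sex, (2) major comorbid axis I diagnosis with two levels (present/absent), and (3) current antidepressant medication status". Each factor has two levels, so there are 2 × 2 × 2 = 8 strata.

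Under Data analysis plan, the primary analysis is set out in some detail: intent-to-treat, ten imputed data sets, imputation models fitted separately by arm, named SAS procedures and a named pooling method. The estimator is given as: "The difference between the CBT and LT groups in the proportions of subjects with a recurrence the next winter will be estimated" for each data set. No stratum or covariate term accompanies it.

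The stratification factors do appear in the imputation step, where sex is among the demographic variables and the list continues with "presence of a comorbid axis I disorder, antidepressant medication status) as potential predictors". Baseline severity scores are used there too. All of these variables return, with treatment interactions, in the secondary modifier regressions.

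The separate imputation models are justified by a pilot finding: "baseline SIGH-SAD scores were negatively correlated with next winter scores in CBT and were positively correlated with next winter scores in LT".

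**The concern.** Stratified blocks largely remove chance imbalance between arms on the three factors. If those factors predict recurrence, the difference in proportions varies less from trial to trial than the usual two-sample standard error assumes. An analysis without a stratum term does not credit this: its interval is wider than it needs to be and its test is conservative. The imputation models do not repair this, because they act only on participants whose next-winter score is missing.

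What is at stake is precision in the one primary comparison. The section on sample size concedes that the true difference may be smaller than the pilot's, and the Discussion rejects designs that need more patients. Stratum adjustment needs no extra patients and no extra data.

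**Working it through.** **1. The plan's own figure.** Inputs from Sample size and statistical power: 52% (LT), 29% (CBT), two-sided alpha 0.05, 80% power, 80 per arm. The mean proportion is 0.405.

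- Uncorrected: n = [1.96·√(2 × 0.405 × 0.595) + 0.8416·√(0.52 × 0.48 + 0.29 × 0.71)]² / 0.23² = (1.3607 + 0.5680)² / 0.0529 = 70.3, so 71 per arm.
- With continuity correction: (70.3/4) × [1 + √(1 + 4/(70.3 × 0.23))]² = 78.8, so 79 per arm.
- Corrected power at 80 per arm: Φ[(0.23 − 1/80 − 1.96 × 0.0776)/0.0755] = Φ(0.866) = 80.7%. Uncorrected: 84.9%.

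The 80 per arm is therefore reproduced by an unadjusted test. The sample size did not rely on adjustment.

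**2. The unadjusted interval.** SE = √[(0.2496 + 0.2059)/80] = 0.0755. Half-width = 1.96 × 0.0755 = 14.8 percentage points.

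**3. Closed form.** If the adjustment variables explain a share R² of outcome variance, the SE is multiplied by √(1 − R²). The article gives no R², so the values below are an assumed range. Power is without continuity correction.

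| Assumed R² | Half-width (points) | Power |
|---|---|---|
| 0 | 14.8 | 84.9% |
| 2% | 14.6 | 85.6% |
| 5% | 14.4 | 86.7% |
| 10% | 14.0 | 88.4% |
| 20% | 13.2 | 91.8% |
| 30% | 12.4 | 94.8% |

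**4. Simulation of the stratified design.** 3,000 trials per scenario; N = 160; blocks of 4 and 6 in 8 strata; no missing data. The plain difference was compared with a linear-model risk difference adjusted for the three factors, with robust SE. The odds ratios are assumed.

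| Odds ratio per factor | Mean half-width, unadjusted → adjusted | 1.96 × actual sampling SD, unadjusted / adjusted | Coverage, unadjusted / adjusted | Rejection rate, unadjusted → adjusted |
|---|---|---|---|---|
| 1 | 14.69 → 14.80 | 14.83 / 14.83 | 94.1% / 94.3% | 85.9% → 85.7% |
| 2 | 14.69 → 14.35 | 14.13 / 14.11 | 95.3% / 95.1% | 87.0% → 88.0% |
| 3 | 14.71 → 13.81 | 13.69 / 13.66 | 96.2% / 94.8% | 87.3% → 90.3% |

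The third column explains the result. Both estimates have almost the same true spread, because stratified allocation has already removed the imbalance. What differs is the reported standard error. At an odds ratio of 3 the unadjusted interval reports 14.71 when the true figure is 13.69.

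The narrowing is 1 − 14.35/14.69 = 2% and 1 − 13.81/14.71 = 6%. In terms of step 3 these match an R² of about 1 − (14.35/14.69)² = 5% and 1 − (13.81/14.71)² = 12%.

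**5. Baseline SIGH-SAD.** Added to the three factors at an odds ratio of 2 each:

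- Same slope in both arms (log odds 0.7 per SD): half-width 14.43 → 13.83, about 4% narrower.
- Equal and opposite slopes (0.7 and −0.7), the sign pattern of the pilot: 14.41 → 14.47, so no gain.
- Opposite slopes with treatment interactions: the reported half-width falls to 13.81, but 1.96 × the sampling SD stays at 14.76 (14.71 with strata alone) and coverage drops to 92.8%. The apparent gain is an understated standard error.

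With 1:1 allocation, the gain for the marginal difference depends on the average of the two slopes, which is near zero when they cancel.

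**The case against.** The strongest reply is that nothing here is wrong. The planned analysis is unbiased, holds its coverage and matches the sample size calculation. The word unadjusted does not occur in the article, and a fuller analysis plan could specify a stratum-weighted difference without contradicting the text. The stratification factors are also not ignored, since they serve the imputation and the modifier analyses.

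Most of this stands. It limits the point to efficiency, and it means that the analysis should not be described as ignoring the strata. It does not remove the point. The article fixes the estimator, the number of imputations, the pooling rule and the software, and its plain reading is a simple difference in proportions. The same analysis is then repeated for three further recurrence definitions.

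Three stronger readings are tempting but unsupported:

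- **That the interval is wider than it need be, whatever the data.** This is true only if the strata predict recurrence, and the article gives no prognostic strengths. Choosing factors for stratification suggests an expectation of relevance; it is not evidence of size.
- **That the test or the sample size is faulty.** Where the strata are prognostic, simulated coverage was 95.3% to 96.2%, so the error is on the conservative side. The 80 per arm is reproduced.
- **That omitting baseline severity wastes precision, because the pilot shows that it predicts outcome.** Baseline SIGH-SAD is not a stratification factor, so leaving it out is no mismatch with the design. The pilot correlations concern continuous scores, their sizes are not given, and their opposite signs point to little or no gain for the marginal difference.

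**Conclusion.** The point holds as a modest, conditional loss of efficiency. The primary estimator as written does not carry the factors on which randomisation is stratified. If those factors predict recurrence, its standard error is conservative. Over assumed odds ratios of 1 to 3 per factor, adjustment narrows the 95% interval by 0% to about 6% (half-width from about 14.7 to at best 13.8 points) and raises power by up to 3 points.

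These figures rest on the planning rates of 52% and 29%, full 80 per arm, and assumed odds ratios. They leave out between-imputation variance, because the article gives no expected missing-data rate. The analysis remains valid if left unchanged.

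**What to change.** In each of the ten imputed data sets, estimate the CBT–LT risk difference adjusted for sex, axis I comorbidity and antidepressant status. Either of these would serve:

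- a Mantel-Haenszel risk difference over the strata, or
- a model with the three factors as main effects, standardised to the whole sample to give a marginal risk difference.

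Pool by the same multiple-imputation rules as now planned, and report the unadjusted difference as a supplement.

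Keep the model small. The pilot's imputed CBT recurrence was 7.0% (Pilot and feasibility studies), which would be about 0.07 × 80 = 5.6 events. A logistic model with arm-specific slopes for several covariates could be unstable at that rate. Baseline SIGH-SAD may be added, but without a claim that it improves precision. If its slope is allowed to differ by arm, the variance must allow for averaging over the observed baseline distribution.

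The cost is a change of wording and slight extra analysis work. All three factors are known before randomisation. If they turn out not to be prognostic, the loss is negligible (simulated half-width 14.8 against 14.7 points).
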